**Figure 1 figure1:**
[figure not shown]
Participant flow chart.

### Measures

Researchers will help the parents/caregivers complete a baseline questionnaire collecting information on COHRQoL using the Early Childhood Oral Health Impact Scale (ECOHIS) for children ≤6 years old [28]. The scale has been evaluated for Australian children and found to have acceptable reliability and validity [29]. We will also collect parent fear levels using the Index of Dental Fear and Anxiety [30] and child dental fear as reported by the parents as well as self-report by children ≥3 years old using the faces scale [31]. Changes in health utility will be evaluated using the generic Child Health Utility 9D Index (CHU_9D) [32], the Euroqol 5D Youth (EQ-5D-Y), and the new oral health specific utility scale planned to be developed in this study. The ECOHIS has been used successfully among Australian Aboriginal population by author LJ in her National Health and Medical Research Council (NHMRC)‒supported research on pregnant Aboriginal women, while the other measures have been used among disadvantaged populations. We will also evaluate the validity of the questionnaires used among this population.

Participant involvement in the proposed study is shown in Table 1. Both test and control groups will complete the same questionnaire on COHRQoL, child dental fear, the CHU_9D, and the EQ-5D-Y, one month after treatment. The test and control groups will also complete the childhood oral health‒related questionnaire and the CHU_9D and the EQ-5D-Y, at the one-month posttreatment, but anchoring their responses to what their child’s oral health was like before the treatment (“Then-test”) to evaluate the possible effects of response shift [33]. Questionnaires on COHRQoL and parent/child fear and anxiety will again be collected at the 12-month follow-up.

We anticipate the clinical examination to take about 10 minutes, and completion of the questionnaire about 30 minutes. ART-based treatment times will vary depending on the extent of treatment required. Treatments may involve multiple appointments, usually about 20 minutes at each appointment. A sample of study participants will be invited to focus group interviews, which will take approximately 1 hour per group.

All participants will also be clinically examined at the 12-month follow-up, by a “blind” calibrated examiner to evaluate their oral health status. Effectiveness will be assessed by the number of teeth treated, dental caries increment, and changes in quality of life. The quality of the treatment provided will be assessed by blind calibrated examiners at follow-up, 12 months after treatment, using established criteria for determining ART restorations [34]. Clinical status of the teeth will be assessed using International Caries Detection and Assessment System-II criteria, which span the continuum from sound to extensive decay [35].

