### A “New” Approach to Dental Caries Management in Early Childhood

The minimally invasive dentistry approach to managing dental caries and its potential role in the provision of public dental services has been described in dental literature [19]. The Atraumatic Restorative Treatment (ART) approach, initially developed to assist dental care delivery in underserved communities, where access to electricity and running water may not be readily available, is now increasingly seen to have relevant applications in subpopulations around the world [20]. Whereas the standard care approach would involve the administration of local anethesia and removal of dental caries using rotary instruments, the ART approach principally relies on removing affected dentine using hand instruments alone, usually without the administration of a local anesthetic, and restoration of the prepared cavity with a glass-ionomer cement. ART makes provision of dental treatment in very young children, where cooperation for standard dental care approach may be limited, feasible in a primary care setting. It may also reduce dental anxiety among children, thereby facilitating appropriate future dental attendance behaviors [21].

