### Outcomes

Primary outcomes are specialist referral and the increment in dental caries. Secondary outcomes are quality of life and acceptability of the ART-based care.

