#### Cost Utility Analysis

Cost-utility analysis will be undertaken using scores derived from the CHU_9D [37,38], the EQ-5D-Y, and the new oral health specific utility scale developed in this study. The use of scores from the CHU_9D as outcome measures in child dental health has been suggested [39]. However, in a preliminary evaluation as an outcome measure it was found not to be sensitive to changes in childhood oral health [40], while the use of the adult version of the EQ-5D has been suggested as being able to differentiate oral health states [41]. Hence, we will further test the usefulness of the CHU-9D as an outcome measure for childhood oral health and seek to develop an oral health specific multi-attribute utility instrument within this project.

**Table 1 table1:** Participant involvement in the proposed study.

Timepoint	Intervention group (test)	Delayed intervention group (control)
Baseline	Questionnaire: ECOHIS, CHU_9D, EQ-5D-Y, Dental Utility Scale, dental fear and anxiety of parent and child; Clinical assessment of children; ART-based care	Questionnaire: ECOHIS, CHU_9D, EQ-5D-Y, Dental Utility Scale, dental fear and anxiety of parent and child; clinical assessment of children; standard care
1 month after baseline treatment	Questionnaire: ECOHIS, CHU_9D, EQ-5D-Y, Dental Utility Scale; child dental fear and anxiety	Questionnaire: ECOHIS, CHU_9D, EQ-5D-Y, Dental Utility Scale; child dental fear and anxiety
6 months after baseline treatment	ART-based care; focus group interviews	Standard care; focus group interviews
12 months after baseline treatment	Questionnaire: ECOHIS, CHU_9D, EQ-5D-Y, Dental Utility Scale; child dental fear and anxiety; clinical assessment	Questionnaire: ECOHIS, CHU_9D, EQ-5D-Y, Dental Utility Scale; child dental fear and anxiety; clinical assessment; ART-based care

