### Treatment Procedures

Test children will be provided with care by dental therapists previously trained in and using the ART approach. Treatment will be undertaken at SDS clinics or field settings, using portable equipment. Restorative treatments will be provided using hand instruments principally, without the use of local anesthesia with the cavity prepared and subsequently restored with a glass-ionomer cement. Where extractions are required, the procedure will be undertaken using standard care approaches. All children will also be provided with preventive fluoride varnish applications at treatment and reviewed at 6-month follow-ups. All treatment will be recorded in patient clinic records. At the 6-month reviews, participants will be provided with preventive fluoride varnish and any other necessary care. Children unable to be provided with care will be referred for specialist care. There will be no direct costs incurred by the participants for the primary care.

Control children will be provided with standard care as part of the fluoride varnish program. Children found to require dental treatment will be referred for care through the prevailing care pathway, that is, government dental services or local private practitioners.

In order to ensure all participants are offered the opportunity to access dental treatment, and in keeping with the delayed treatment intervention design, control participants will be offered treatment using the test treatment approach after the 12-month follow-up.

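### The 12-month caries reading is called blind, but the design does not secure this: ART is trial care in one arm only, and whole communities share an allocation

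*Protocol article*

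**What the plan says.** Under Outcomes: "Primary outcomes are specialist referral and the increment in dental caries". The increment needs a reading at baseline and one at 12 months.

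Measures describes the second reading: "All participants will also be clinically examined at the 12-month follow-up, by a “blind” calibrated examiner to evaluate their oral health status". It names the instrument: "Clinical status of the teeth will be assessed using International Caries Detection and Assessment System-II criteria", a scale that the article says runs from sound teeth to extensive decay. A separate sentence says that treatment quality "will be assessed by blind calibrated examiners at follow-up, 12 months after treatment, using established criteria for determining ART restorations".

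Treatment Procedures describes test-arm care: "Restorative treatments will be provided using hand instruments principally, without the use of local anesthesia with the cavity prepared and subsequently restored with a glass-ionomer". Control children receive fluoride varnish and, if they need treatment, referral to government services or private practitioners. They are offered the test approach after the 12-month follow-up. Table 1 lists, for the control group at 12 months: "child dental fear and anxiety; clinical assessment; ART-based care".

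Recruitment allocates whole communities, at least 50 km apart, stratified partly on caries found at the baseline examination.

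**The concern.** The article makes an affirmative claim of blinding for the examination behind a primary outcome. Other parts of the same article work against it. The treatment leaves a visible trace, "restoration of the prepared cavity with a glass-ionomer cement", and before the 12-month visit the trial places that trace in one arm only. Criteria written for ART restorations direct attention to that trace. Because allocation is by community, a cue from one child bears on every child there, including those with no filling.

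At stake is the follow-up half of the caries increment. Scoring early lesions takes judgement, and an examiner who has inferred the arm may score more leniently or more strictly. A cue shared by a whole community would push its readings in one direction, so the error would not average out over children. Reporting the result as blind would overstate its protection from bias.

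**Working it through.** **Setting the sections side by side**

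| Question | Test arm | Control arm | Source |
|---|---|---|---|
| ART as trial care before the 12-month visit? | Yes | No | Treatment Procedures; Table 1 |
| Other restorative care before 12 months | Hand instruments principally, so not exclusively | Referral to government or private care; government clinics usually use local anesthetic and rotary instruments | Treatment Procedures; Current Situation |
| Restoration material | Glass-ionomer | Not given | Treatment Procedures; Current Situation |
| Unit of allocation | Whole community | Whole community | Recruitment |
| Grading criteria at follow-up | Specific to ART | Specific to ART | Measures |

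ART restorations recurring across a community are strong evidence that it is a test community. One filled child is weaker evidence, because control children may have outside fillings of unstated material.

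**Which parts of the primary outcomes are exposed.** Baseline caries is used to stratify the randomization, so that reading precedes allocation. Specialist referral is not shown to depend on this examiner. That leaves the 12-month caries reading.

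**How likely is a cue?** The masking statement carries no figure, so there is none to reproduce. The cluster size comes from Sample Size: 220 per arm × 0.75 = 165, and 165 / 15 communities = 11 children seen at follow-up.

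Let p be the probability that a test child shows a recognisable ART restoration. The documents do not give p; 0.10 to 0.30 is assumed. With children treated as independent, the chance of at least one such child in a test community is 1 − (1 − p)^11:

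- p = 0.10: 1 − 0.9^11 = 0.69
- p = 0.20: 1 − 0.8^11 = 0.91
- p = 0.30: 1 − 0.7^11 = 0.98

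This counts communities with a cue, not examinations affected. If children are seen in sequence, the expected share of test-arm examinations made at or after the first cue is the mean of 1 − (1 − p)^j over j = 1 to 11, which is 44%, 67% and 79%. Both sets of figures treat recognition as certain, so they are upper-end illustrations.

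**What could a scoring shift do?** This is also an illustration. Apply the plan's ICC of 0.05 and 11 per cluster to a standardized caries difference: design effect = 1 + (11 − 1) × 0.05 = 1.5, and SE = √(2 × 1.5 / 165) = 0.135 SD. For a differential shift of b SD between arms with no true effect, two-sided type I error = 1 − Φ(1.96 − b/SE) + Φ(−1.96 − b/SE):

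- b = 0.05: 6.6%
- b = 0.10: 11.5%
- b = 0.20: 32%

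The values of b are assumed. Nothing in the documents says how large a shift would be, or in which direction.

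**The case against.** The strongest reply is that an article condenses the full protocol. Examination order, separation of examiners and forms for guessing allocation commonly sit in a full protocol or examiner manual, so their absence here is no defect. That stands. What remains is the claim itself: the article states that the examination is blind, while the features it describes make this hard to sustain.

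Several stronger readings are tempting, and the documents do not support them.

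- **One examiner must do both tasks.** A reader might infer this from the single 12-month clinical assessment in Table 1. Measures speaks of one examiner for the oral examination and of examiners, plural, for grading, and does not say they are the same. The point does not need it: a caries examiner who grades nothing still sees the restorations.
- **Applying ART criteria proves the arm.** Private practitioners' technique and the material used in standard care are not given. The documents do not say that use of a drill or anesthetic can be seen in a finished restoration.
- **A treatment team at the control visit reveals the arm.** Table 1 puts ART-based care at the 12-month timepoint, but Treatment Procedures puts it after the follow-up, and nowhere is a team placed at the examination. The two places need reconciling; they do not show unmasking.
- **Restoration quality lacks a comparison between arms.** It is not a listed outcome and no hypothesis compares it. The grading reads as a check on the treatment provided, so this is not a defect.
- **The cue is close to certain.** Using 15 children per community gives 79% to over 99% for the same p, but 15 is the number enrolled; 11 are expected after loss.

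**Conclusion.** The point holds in a limited form. Masking of the 12-month caries reading is stated but not secured, and is unlikely to hold fully. A reader might conclude that the blind has failed outright. That goes too far, because it is an inference from the design and the full protocol may hold safeguards.

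The exposure is confined to the follow-up half of one primary outcome. Its size cannot be derived from the documents. The 69% to 98% range rests on an assumed p of 0.10 to 0.30, 11 independent children per community and certain recognition, and look-alike control fillings would lower it. The type I error figures rest on assumed scoring shifts and show only that a modest shift would matter. The issue deserves correction because the remedy is cheap and a primary outcome is involved.

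**What to change.** In Measures:

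1. Describe the examiner as not told the allocation, with masking where possible, in place of the unqualified claim.
2. Record and close each child's ICDAS-II caries scores, with one common code for any restoration, before any restoration is graded. This stops the ART criteria from prompting the caries score. It does not hide the restorations, so it limits the problem without removing it.
3. Have the examiner record a guess of the allocation, so that the degree of unmasking can be reported.
4. Add a supporting analysis of the increment at the cavitated-lesion threshold, where scoring depends least on judgement.

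Reconcile Table 1 with Treatment Procedures so that both make clear that the 12-month outcome examination comes before delayed ART, the order that Treatment Procedures already states.

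The cost is a weaker masking claim, changes to the wording and the examination form, and a few more minutes of recording per child. No extra staff are needed.

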### Economic Evaluations

#### Cost-Effectiveness Analysis

Cost-effectiveness of the intervention will be estimated using standard approaches [36] and will be from a health care provider perspective. Effectiveness measures will be the number of children managed in primary care without need for specialist referral, changes in COHRQoL, the numbers and types of treatments provided, and dental caries increments. The economic evaluation will compare any incremental costs of the intervention (ie, costs accrued in the intervention arm compared to those in the control arm) to the full list of incremental primary and secondary outcome endpoints, all expressed in their natural units of measurement. Costs will be measured from activity data with pathway analysis to fully specify all activities in both intervention and control arms. The resource use and dental services utilization will be obtained from research team records and intervention provider records. Measured resource use will be valued using both existing estimates of the costs of each unit of the resource use from market prices and the Dental Benefit Schedule fee rates for nonspecialist and specialist attendances. Standard discounting will be applied to both cost and outcomes. Uncertainty in the cost and outcome data will be subjected to sensitivity analyses.

#### Cost Utility Analysis

Cost-utility analysis will be undertaken using scores derived from the CHU_9D [37,38], the EQ-5D-Y, and the new oral health specific utility scale developed in this study. The use of scores from the CHU_9D as outcome measures in child dental health has been suggested [39]. However, in a preliminary evaluation as an outcome measure it was found not to be sensitive to changes in childhood oral health [40], while the use of the adult version of the EQ-5D has been suggested as being able to differentiate oral health states [41]. Hence, we will further test the usefulness of the CHU-9D as an outcome measure for childhood oral health and seek to develop an oral health specific multi-attribute utility instrument within this project.

**Table 1 table1:** Participant involvement in the proposed study.

Timepoint	Intervention group (test)	Delayed intervention group (control)
Baseline	Questionnaire: ECOHIS, CHU_9D, EQ-5D-Y, Dental Utility Scale, dental fear and anxiety of parent and child; Clinical assessment of children; ART-based care	Questionnaire: ECOHIS, CHU_9D, EQ-5D-Y, Dental Utility Scale, dental fear and anxiety of parent and child; clinical assessment of children; standard care
1 month after baseline treatment	Questionnaire: ECOHIS, CHU_9D, EQ-5D-Y, Dental Utility Scale; child dental fear and anxiety	Questionnaire: ECOHIS, CHU_9D, EQ-5D-Y, Dental Utility Scale; child dental fear and anxiety
6 months after baseline treatment	ART-based care; focus group interviews	Standard care; focus group interviews
12 months after baseline treatment	Questionnaire: ECOHIS, CHU_9D, EQ-5D-Y, Dental Utility Scale; child dental fear and anxiety; clinical assessment	Questionnaire: ECOHIS, CHU_9D, EQ-5D-Y, Dental Utility Scale; child dental fear and anxiety; clinical assessment; ART-based care

### Dental Specific Multi-Attribute Utility Instrument and a New Dental Utility Scale

We will use the available dataset of ECOHIS from the 250 respondents in the recently completed WA pilot study [29]. Although valid and widely used, available quality of life instruments in oral health cannot be used to measure quality-adjusted life years (QALYs). We will use the methodology described by Brazier and Rowen et al [42,43] to guide the development of the new oral health specific preference-based instrument. This includes a six-stage approach: establish dimensionality (Stage 1), eliminate and select items per dimension (Stage 2), explore item-level reduction (Stage 3), validate instruments (Stage 4), apply the new instrument to elicit health state values for a sample of health states described (Stage 5), and analyze the model results to produce utility values for all health states (Stage 6). The new Dental Utility Scale will then be developed.

This will be the first multi-attribute utility instrument in oral health conditions as well as the first validated multi-attribute utility instrument in this age group. This new instrument and its scale will be used to calculate QALYs for the cost-utility analysis.

### Treatment Procedures

Test children will be provided with care by dental therapists previously trained in and using the ART approach. Treatment will be undertaken at SDS clinics or field settings, using portable equipment. Restorative treatments will be provided using hand instruments principally, without the use of local anesthesia with the cavity prepared and subsequently restored with a glass-ionomer cement. Where extractions are required, the procedure will be undertaken using standard care approaches. All children will also be provided with preventive fluoride varnish applications at treatment and reviewed at 6-month follow-ups. All treatment will be recorded in patient clinic records. At the 6-month reviews, participants will be provided with preventive fluoride varnish and any other necessary care. Children unable to be provided with care will be referred for specialist care. There will be no direct costs incurred by the participants for the primary care.

Control children will be provided with standard care as part of the fluoride varnish program. Children found to require dental treatment will be referred for care through the prevailing care pathway, that is, government dental services or local private practitioners.

In order to ensure all participants are offered the opportunity to access dental treatment, and in keeping with the delayed treatment intervention design, control participants will be offered treatment using the test treatment approach after the 12-month follow-up.

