### Current Situation

The WA state government is introducing an early childhood preventive program for preschool children (0-4-year-olds) in rural and remote Aboriginal communities by applying fluoride varnish to the primary teeth by Aboriginal health workers trained in the fluoride varnish application. The fluoride varnish program is incrementally being rolled out throughout WA, starting in Kimberley (north-west WA) in 2016. The program is a preventive program, and children requiring dental treatment are referred to the local dental practitioners, either private practitioners or practitioners within the Health Department or Aboriginal Medical Services. While fluoride varnish application has been shown to be efficacious in ECC prevention among Aboriginal children [26], children without adequate access to treatment services may continue to experience untreated disease.

Currently, preschool children (ineligible for SDS care) requiring dental treatment need to source care from private dental practitioners (ie, at their own cost) or, if eligible for subsidized care (ie, liable for co-payments) through government general dental clinics, where restorative care is provided by dentists. Dental therapist and oral health therapists provide mainly dental hygiene services. Subsidized dental care is available to those who are in receipt of certain types of Commonwealth Government benefits (eligibility for the benefits are means tested). The WA government general dental clinics, located mainly in regional cities and major towns, provide clinical care mainly to eligible adults, but children ineligible for SDS and in receipt of specific types of government benefits are able to access care. The location of these clinics in major regional centers means extensive travel for children living in more remote locations to access care. Also, treatment is usually provided using standard care approaches involving the administration of a local anesthetic and using rotary instruments to prepare the cavity.

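### Specialist referral is decided by unmasked providers who differ by arm, so a referral rate alone cannot show that children were successfully managed; a common 12-month supportive outcome is needed.

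*Protocol article*

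**What the plan says.** Under Outcomes: "Primary outcomes are specialist referral and the increment in dental caries". Sample Size is built on referral alone: 10% against 25%, with an intracluster correlation of .05.

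Under Treatment Procedures, "Test children will be provided with care by dental therapists previously trained in and using the ART approach", and later in the same paragraph "Children unable to be provided with care will be referred for specialist care". For control, "Children found to require dental treatment will be referred for care through the prevailing care pathway, that is, government dental services or local private practitioners". The Current Situation section adds that subsidised care for these children runs "through government general dental clinics, where restorative care is provided by dentists".

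Masking appears under Measures. All participants are seen at 12 months "by a “blind” calibrated examiner to evaluate their oral health status", and treatment quality is also read blind. No masking is stated for referral.

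The Aim 1 hypothesis goes further than a referral count: it concerns children who are managed successfully with neither a referral nor new caries. Referral also enters the cost-effectiveness analysis as an effectiveness measure.

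**The concern.** A referral is a provider's decision, not a measurement of the child. In the test arm it is made within the care that the ART therapists deliver. In control it is made, if at all, by practitioners in other services. A provider who gives ART cannot be masked to it.

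A lower test-arm rate therefore has at least two readings: needs were met in primary care, or the therapists were less ready to refer. A low control rate has a further one: Aboriginal Oral Health and Current Situation describe poor access and long travel, and a child who never reaches a practitioner cannot be referred by one.

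At stake is the meaning of the Aim 1 result and of the cost-effectiveness ratio. In both, a child with unmet need who was not referred counts as a gain.

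**Working it through.** **1. The plan's own figure.** Inputs from Sample Size: 10% against 25%, ICC .05, 15 clusters per arm, 80% power, alpha .05 (two-sided assumed).

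- Design effect at 11 children per cluster: 1 + (11 − 1) × .05 = 1.5.
- Standard error at 165 per arm: √[(0.10 × 0.90 + 0.25 × 0.75) × 1.5 / 165] = 0.0502.
- Signal: 0.15 / 0.0502 = 2.99. With a t-test on 2 × (15 − 1) = 28 df, power is 82.2%. With 10 children per cluster it is 79.8%, so 11 is the smallest cluster size that reaches 80%. This gives 15 × 11 = 165.
- Allowing for loss: 165 / 0.75 = 220.

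The stated 165 and 220 reproduce. The sample size itself is not in question.

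**2. What the referral rate can absorb.** The documents give no referral thresholds and no attendance rates, so everything in this step is assumed. Let 25% of children in each arm need referral by one common standard, and let ART have no true effect. Let r be the readiness of test-arm providers to refer, relative to control, and let a be the share of control children in need who reach a provider.

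Observed test rate = 0.25 × r. Observed control rate = 0.25 × a.

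| r | a | Test | Control | Apparent result |
|---|---|---|---|---|
| 0.8 | 1 | 20% | 25% | favours test |
| 0.6 | 1 | 15% | 25% | favours test |
| 1 | 0.8 | 25% | 20% | favours control |
| 1 | 0.6 | 25% | 15% | favours control |
| 0.6 | 0.6 | 15% | 15% | no difference |

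With the standard error of step 1, 20% against 25% is significant with probability about 14%, and 15% against 25% with about 44%. The nominal figure in that one direction is 2.5%. The formula is symmetric, so the access rows carry the same probabilities in the opposite direction.

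**3. Whether the pilot settles it.** The pilot rates of 5% and 49% (Sample Size) come from ART-trained therapists compared with dentists (Evidence). The decider differed by arm there too, so those rates cannot separate the readings either.

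**4. What a common 12-month criterion does.** Count a child as not managed if referred, or if untreated cavitated decay is present at the blind examination. Let s be the share of unreferred need that is visible as such decay, and hold all other decay equal between arms. The failure rate is then 0.25 × [r + (1 − r) × s] in test, and the same with a in control.

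- s = 1: 25% in both arms for every row of the table. The spurious difference disappears.
- s = 0.5, r = 0.6, a = 1: 0.25 × (0.6 + 0.2) = 20% against 25%. The gap of 10 points halves to 5.

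The criterion works in both directions, but only as far as unmet need shows as decay.

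**The case against.** The strongest reply is that this difference is the intervention. The trial compares a therapist-delivered ART model with existing care, and managing more children without referral is the hypothesised mechanism. That stands: readiness to refer and true benefit are confounded, and the planned effect is not shown to be false.

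Second, the plan already holds a check. Caries increment is also a primary outcome, and oral health status and treatment quality are read blind at 12 months. That stands in part. These data can expose unmet need, but the plan as written does not join them to referral in one measure defined alike in both arms.

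Third, referral criteria may sit in a fuller protocol. The point does not rest on their absence. It rests on what is stated: different providers by arm, and masking confined to the examination. It is an inference that the treating therapist judges who cannot be treated, since the sentence names no decider, but its place in the paragraph on therapist care makes that the natural reading.

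A reader might infer more than the documents support:

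- **That readiness to refer could explain the whole planned effect.** This needs r = 0.10 / 0.25 = 0.40 with full access in control. No document figure supports either condition, and poor access pulls the other way.
- **That the therapists were trained by the trial and have a stake in its result.** The text says only that they were already trained in ART and use it.
- **That shared therapists inflate the variance beyond the community design effect.** Neither the number of therapists nor a therapist-level correlation is given, so no figure can be put on this.
- **That comparing referral only among children with high need at baseline would cure the problem.** The same arm-specific provider still makes the decision.

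**Conclusion.** The point holds in a limited form. The referral outcome is decided by unmasked providers who differ by arm, and on its own it does not measure the successful management that Aim 1 names. The blind 12-month examination is a partial check that the plan does not yet use for this purpose.

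The net direction of bias is unknown. Its size cannot be estimated from the documents: the range in the working (apparent differences of 5 to 10 points either way, or none) rests on an assumed 25% common need, on no true effect and on assumed readiness and access. This calls for an added analysis. It is no reason to replace the primary outcome.

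**What to change.** In Data Analysis, keep referral as the primary outcome and add one pre-specified supportive analysis:

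- **Definition, identical in both arms:** successfully managed means not referred to a specialist and with no untreated cavitated decay on the ICDAS-II codes recorded by the blind examiner at 12 months. Control children are offered ART only after that follow-up, so the reading precedes delayed treatment.
- **Analysis:** the same cluster-adjusted model as for referral, adjusted for baseline caries, and reported beside the referral result.
- **Economics:** use it as an alternative effectiveness measure in the cost-effectiveness analysis.
- **Interpretation:** if the two results disagree, do not claim that referral alone shows that need was met.

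Nothing changes in who is referred or treated. The cost is one derived variable and a little more analysis from data already planned.

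Two limits should be stated with it. ICDAS-II does not capture a child's cooperation, so the ambiguity is reduced and not removed. The measure also counts new decay, and decay left by poor access, as not managed, so it answers a broader question than referral and belongs beside it as supportive.
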